## Abstract

**Background:**

First-line pharmacotherapy for neuropathic pain entails the use of systemic antidepressants and anticonvulsants. These drugs are not optimally effective and poorly tolerated, especially for older patients with comorbid conditions. Given the high number of such patients, there is a need for a greater repertoire of safer and more effective analgesics. Clonidine and pentoxifylline are vasodilator agents that work synergistically to enhance tissue perfusion and oxygenation. The topical administration of these drugs, individually and in combination, has shown anti-nociceptive properties in rodent models of neuropathic pain. A topically-administered combination of clonidine and pentoxifylline also effectively reduced the intensity of both spontaneous and evoked pain in healthy volunteers with experimentally-induced neuropathic pain. The next step in advancing this formulation to clinical use is the undertaking of a phase II clinical study to assess its efficacy and safety in neuropathic pain patients.

**Methods/design:**

This is a study protocol for a randomized, double-blind, placebo-controlled, phase II clinical trial with a cross-over design. It is a single-centered, 5-week study that will enroll a total of 32 patients with post-traumatic peripheral neuropathic pain. Patients will be treated topically with either a combination of clonidine and pentoxifylline or placebo for a period of 2 weeks each, in randomly assigned order across patients, with an intervening washout period of 1 week. The primary outcome measures of the study are the intensity of spontaneous pain recorded daily in a pain diary with a visual analog scale, and the degree of mechanical allodynia evoked by a brush stimulus. The secondary outcome measures of the study include scores of pain relief and change in the area of punctate hyperalgesia. This trial has been prospectively registered with ClinicalTrials.gov on November 1, 2017. ClinicalTrials.gov Identifier: NCT03342950.

**Discussion:**

The analgesic use of topical treatment with clonidine and pentoxifylline in combination has not been investigated in post-traumatic neuropathic pain. This study could generate the first evidence for the efficacy and safety of the formulation in alleviating pain in patients with neuropathic pain. Furthermore, this trial will provide objective grounds for the investigation of other agents that enhance tissue oxygenation in the topical treatment of peripheral neuropathic pain.

**Trial registration:**

This trial has been registered with ClinicalTrials.gov owned by NIH’s US National Library of Medicine.

ClinicalTrials.gov NCT03342950. Registered on November 1, 2017 (trial was prospectively registered).

**Protocol version and identifiers:**

This is protocol version 5, dated June 2018. McGill University Health Center (MUHC) Reaseach Ethics Board (REB) identification number: TTNP 2018-3906.

## Background

Peripheral neuropathic pain is a chronic pain condition that is a direct outcome of damage to the peripheral nerves [1]. The damage could result from a myriad of etiologies like physical trauma, metabolic dysfunctions like diabetes mellitus, or toxic effects of chemotherapeutic agents [2]. The patients suffer from debilitating pain of burning, tingling, or electric shock-like quality, along with hypersensitivity to touch, pressure, and changes in temperature [2]. Although the pathophysiology of peripheral neuropathic pain involves an interplay between neuronal, immune, neuroimmune, vascular, and metabolic factors, first-line pharmacologic analgesics in clinical use are mostly antidepressants and anticonvulsants that solely target modulatory processes in the central nervous system [3]. In addition to being sub-optimally therapeutic, these agents have significant side effects often making them intolerable especially to patients of older age and co-morbid conditions [4, 5]. There is an indisputable need for effective and safe analgesic options for patients with peripheral neuropathic pain.

Peripheral neuropathic pain of varying etiologies involves microvascular changes that result in ischemic hypoxia of the affected nerves. Functionally, deficits have been reported in the endothelial production of vasodilatory nitric oxide (NO), which normally acts to counteract the basal vasoconstrictive sympathetic tone [6]. Structural changes to the endoneurial vessels have also been observed, including endothelial cell layer swelling and capillary basement membrane thickening [7, 8]. These microvascular changes impair endoneurial nutritive perfusion and oxygenation, which can directly impact the excitability of the peripheral nerves [9]. The tactile allodynia and thermal hyperalgesia exhibited by neuropathic rats are significantly correlated to the extent of endoneurial hypoxia in the affected peripheral nerves [10, 11]. Therefore, treatments aimed at enhancing tissue oxygenation by increasing arterial and capillary flow may effectively relieve symptoms in patients with neuropathic pain.

Microvascular perfusion is under the regulation of vasodilatory molecules produced by the endothelium like NO and the vasoconstrictive transmitter norepinephrine, which is released from sympathetic post-ganglionic neurons [12, 13]. NO’s vasodilator effect occurs by the augmentation of vascular smooth muscle cyclic mononucleotide level that in turn inhibits calcium influx and smooth muscle contraction, a mechanism that is counterbalanced by the activity of phosphodiesterase enzymes that degrade cyclic mononucleotides [14]. Drugs with phosphodiesterase inhibitor activity, including pentoxifylline, produce vasodilation and enhance blood flow [15, 16]. Primarily indicated for peripheral arterial disease, pentoxifylline inhibits a broad isoform of phosphodiesterase enzymes resulting in enhanced blood flow, reduced platelet aggregation, decreased blood viscosity, and increased red blood cell flexibility, all of which aid in alleviating poor microvascular perfusion [16–18]. On the other hand, microvascular perfusion is further degraded by the vasoconstrictive effect of sympathetic activity when norepinephrine binds to α-adrenergic receptors on vascular smooth muscle cells [19]. Clonidine is a drug that counteracts sympathetic vasoconstriction by activating presynaptic α_2_-adrenergic receptors and reducing the release of norepinephrine both centrally and at peripheral sympathetic nerve endings [20]. It has also been reported to activate endothelial α_2_-receptors resulting in increased release of NO and subsequent vasodilation [21]. Therefore, clonidine and pentoxifylline act via complementary mechanisms to increase microvascular caliber, blood flow, and tissue perfusion.

In neuropathic pain, the effects of microvascular dysfunction are most adverse on the peripheral nerve’s distal endings in the skin, also called intraepidermal nerve fibers [22, 23]. Thus, topical microvascular-targeted local and cutaneous interventions that are effective in combating poor nutritive perfusion of the peripheral nerve endings are beneficial. The topical route allows the delivery of effective drugs in high concentrations at the local target site while avoiding undesired systemic and adverse effects [24]. Prior studies by our group have demonstrated that topical combination of α-adrenergic receptor agonists and phosphodiesterase inhibitors effectively alleviate tactile allodynia and microvascular dysfunction in rodent models of post-traumatic, diabetic, and chemotherapy-induced neuropathic pain [25]. α_2_-Adrenergic receptor agonists have also been used topically to alleviate chronic pain in humans [26, 27]. Moreover, as an initial step in determining the translatability of topical combination of clonidine and pentoxifylline as analgesics, we have tested the effect of the formulation in healthy volunteers in an experimentally-induced surrogate for neuropathic pain using a double-blind randomized and controlled design [28]. In the study, an experimental model of neuropathic pain was induced by tourniquet exposure following intradermal capsaicin injection. Subsequent topical treatment with the combination of clonidine and pentoxifylline significantly reduced the superficial and deep “neuropathic-like” pain reported by the volunteers. Moreover, areas of dynamic allodynia and mechanical hyperalgesia were significantly reduced to an extent that exceeded the published effectiveness of most analgesics, including opioids and gabapentinoids [29, 30]. The current protocol aims to examine the second translational investigative level to determine the effectiveness and safety of the same topical combination of clonidine and pentoxifylline in relieving pain in patients with post-traumatic neuropathic pain.

## Objectives

The main focus of this phase II proof-of-concept clinical trial is to provide preliminary evidence for the analgesic efficacy and safety of the topical combination of clonidine and pentoxifylline on post-traumatic neropathic pain using a small and well-defined patient population. More specifically, the study will measure the magnitude of relief of spontaneous pain produced by the treatment using daily recordings of pain level with visual analog scale (VAS)-based pain diaries. To estimate the effect of the treatment on evoked pain, measures for severity of dynamic mechanical hyperalgesia and area of punctate hyperalgesia will also be assessed.

## Methods

### Trial design

This trial uses a randomized, double-blind, placebo-controlled cross-over study design. In this counterbalanced cross-over study, enrolled patients will be treated with active drug and placebo for periods of 2 weeks each, with an intervening 1-week washout period (Fig. 1).

**Fig. 1 Fig1:**
[figure not shown]
Study flow chart

### Study setting

This is a single-center study taking place in the Alan Edwards Pain Management Unit at the Montreal General Hospital, Montreal, Quebec. The study has been authorized by the McGill University Health Centre Research Ethics Board (TTNP: 2018-3906) and Health Canada (control number: 201880). Moreover, it is registered with NIH’s US National Library of Medicine database: ClinicalTrials.gov (Identifier: NCT03342950).

### Study process

A summary of the study process is outlined in Table 1. The first screening visit will entail obtaining informed consent; reviewing patients’ medical history, including the patients’ current medications; performing sensory tests for mechanical sensitivity; collecting blood samples for liver and kidney function; and obtaining urine samples from pre-menopausal women for a pregnancy test. Patients will be provided with a pain diary to record their daily pain intensity for the 7 days that follow the screening visit. Patients with normal laboratory test results of liver and kidney function will be contacted over the phone. After the assessment of pain diaries for pain intensity, patients that meet the eligibility requirements of the study (see below) will be provided with study drugs according to the treatment regimen assigned for the first 2 weeks of the trial. Regular medications used before enrolment into the study will be continued.

**Table 1 Tab1:**
[figure not shown]
Study process

Throughout each treatment period and during the washout, patients will be asked to record their average pain scores in a pain diary, once daily in the evening. At the beginning and end of each treatment block, sensory testing will be performed to determine the degree of dynamic mechanical allodynia and area of punctate hyperalgesia. At the end of each treatment block, patients will be asked to score the degree of their overall pain relief. Adverse events will also be captured at the end of each treatment block and after the washout week.

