### Randomization and blinding

Randomization for treatment order (placebo–active drug/active drug–placebo) is performed by a coin flip done by a research coordinator assigned for this task who is not involved in patient interaction and outcome assessment. The same coordinator also ensures blinding by assigning a three-digit number code, from a computer-generated random list, to the Topi-Pumps used in each treatment block. The list of number codes and the identity of their corresponding treatment is only shared with the compounding pharmacy. The blinding applies to the patient, the study coordinator performing patient assessments, and the dispensing pharmacy.

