### Safety and adverse event outcomes

Both clonidine and pentoxifylline have a history of safe systemic use in humans, and there is evidence that topical application of these agents produces extremely low to undetectable plasma levels [27]. As no negative effects were observed in animals or adverse effects in our trial in healthy volunteers, we do not anticipate any adverse side-effects with our topical treatment [25, 28].

According to the FDA, rare events in patients taking pentoxifylline (although not established as caused by the drug) include anaphylactic reactions [32]. Subjects will be asked to immediately report any signs of anaphylaxis (itchy rash, lip or throat swelling) to the study coordinator, who will instruct the patient to go immediately to a hospital emergency room.

Risks involved in taking clonidine orally are dizziness, light-headedness, drowsiness, tiredness, and vision problems, which are caused by a decrease in blood pressure [33]. Patients will be asked to immediately report any of these symptoms to the study coordinator, who will instruct the patient to see the study physician, who will perform a medical evaluation, including assessment of blood pressure. If any subject’s systolic pressure is found to be below 80 mmHg, they will be asked to stop the treatments and will be removed from the study. Abrupt discontinuation of clonidine can occasionally result in a withdraw syndrome, characterized by a rebound increase in blood pressure and other symptoms and signs of sympathetic activity like restlessness, increased heart rate, and increased irritability [34]. This usually occurs after cessation of large oral doses and in some instances after transdermal treatment. There is minimal risk for this syndrome with our study drug, as the dose of clonidine used is much lower than oral or transdermal preparations. Patients will be asked to report to the study coordinator if any of these symptoms occur during the washout period of the study and the few days following completion of the study. Clinical evaluation and appropriate medical care will accordingly be provided.

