### Endpoints and post-trial care

Eligible patients are expected to have stable disease with no alteration to their treatment regimen in the 5 weeks preceding enrollment. If a patient develops uncontrolled pain with a clinical indication for a new treatment during the study period, the participation of the patient in the trial will be discontinued and the new treatment commenced. If any subject’s systolic pressure is found to drop below 80 mmHg during any section of the trial, they will be asked to stop the treatments and they will be removed from the study. Finally, in the event of an anaphylactic reaction to any of the topical treatments used in the study, the patient’s participation in the study will immediately be terminated. In both instances, the coordinator performing the randomization will send the study physician the information required to unblind him to the study drug the patient was taking so the information can be transferred to the medical team that will care for the patient.

Patients will be instructed to contact the study coordinator and/or physician if symptoms of clonidine withdrawal occur during washout or the week following completion of the study. In such an event, the study physician will perform a clinical evaluation of the patient and appropriate medical care will be provided. Unblinding and termination of participation in the study will depend on the study physician’s assessment of the patient’s clinical status.

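### In the visible text, scheduled adverse-event capture stops at the end of block 2, so events after stopping active drug are solicited only in active-first patients; separately, two sections give different windows for reporting withdrawal symptoms

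*Protocol article*

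**What the plan says.** Under Trial design, patients are "treated with active drug and placebo for periods of 2 weeks each, with an intervening 1-week washout period". The abstract gives the overall frame: "It is a single-centered, 5-week study that will enroll a total of 32 patients". Treatment order "is performed by a coin flip done by a research coordinator" (Randomization and blinding).

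Study process fixes when adverse events are collected: "Adverse events will also be captured at the end of each treatment block and after the washout week". The visible text names no later scheduled contact.

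Safety and adverse event outcomes names the risk that matters after treatment stops: "Abrupt discontinuation of clonidine can occasionally result in a withdraw syndrome, characterized by a rebound increase in blood pressure". It calls this risk minimal for the study drug and asks patients to tell the coordinator if such symptoms "occur during the washout period of the study and the few days following completion of the study". Endpoints and post-trial care gives the same instruction, but for symptoms that "occur during washout or the week following completion of the study". In both sections a report leads to clinical evaluation and care. In the second, unblinding and withdrawal from the study then depend on the study physician's assessment.

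**The concern.** There are two separate defects, and neither causes the other.

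The first is one of collection. The protocol identifies a risk that arises after clonidine is stopped, but its capture schedule reaches past the stopping point for one sequence only. An active-first patient stops at week 2 and is asked about events after the washout. A placebo-first patient stops active drug at week 5, when the last capture takes place, and from then on must volunteer any symptom. Safety is one of the trial's stated objectives, and all adverse events are to be tabulated and reviewed. Without a marker, that table would mix answers to a scheduled question with unprompted reports. An absence of withdrawal events in the second sequence would be weaker evidence than the same absence in the first.

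The second is one of consistency. One instruction to patients has two different end points in two sections. Staff following one section will tell patients something different from staff following the other, and a symptom late in the first week after completion falls inside one window and possibly outside the other.

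**Working it through.** **Timeline.** Inputs: two blocks of 2 weeks and a 1-week washout (Trial design). The sum 2 + 1 + 2 = 5 weeks reproduces the abstract's study length. Placing the scheduled captures on it:

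| Scheduled capture | Week | Active-first patient | Placebo-first patient |
|---|---|---|---|
| End of block 1 | 2 | on active, about to stop | on placebo |
| After washout | 3 | one week after stopping active | one week after stopping placebo |
| End of block 2 | 5 | on placebo | on active, about to stop |
| Later | none listed | self-report only | self-report only, first time off active |

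Only the active-first column has a scheduled capture soon after active drug stops.

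**How many patients.** With 32 patients and independent fair coin flips (assumed), the number given active drug first follows Binomial(32, 0.5). The mean is 32 × 0.5 = 16, and the 2.5% and 97.5% points are 10 and 22. Trial design also calls the study counterbalanced. If that means an enforced equal split, the number is exactly 16.

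**What a clean result would show.** If none of n solicited patients has a withdrawal event, the one-sided 95% upper bound on the true rate is 1 − 0.05^(1/n):

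- n = 16: 1 − 0.05^(1/16) = 17.1%
- n = 32: 1 − 0.05^(1/32) = 8.9%
- n = 10: 25.9%; n = 22: 12.7% (the ends of the coin-flip range)

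These ignore dropout. If only the 27 patients required by the sample-size section were available, full coverage would give 10.5%, and 13 solicited patients (about half of 27) would give 20.6%. The ratio of roughly two to one is unchanged.

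The comparison of 17.1% with 8.9% treats the scheduled question as catching every event and self-report as catching none. At the 16/16 split it is therefore the upper limit of what is lost, not an estimate.

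**The two windows.** Both safety sections cover the washout and a period after completion, and both rely on the patient to make contact. They differ only in the period after completion: a few days, which is not a defined length, in one, and a week in the other. No arithmetic applies; the text must be reconciled.

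**The case against.** The strongest reply is that the full schedule cannot be seen. Table 1, which summarises the study process, is not shown, and the article condenses a longer protocol that may include a post-study contact. The 5-week figure does not settle this: the 7-day screening diary already lies outside it, so a later call could too. This stands as a limit. The point is about the visible text, and there the sentence in Study process states when events are captured and stops at block 2. If Table 1 does hold a later contact, that sentence needs correcting.

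Second, patients in both sequences are told to report withdrawal symptoms, and reports lead to evaluation. This also stands. Active-second patients are not unmonitored; they lack only the scheduled question. The protocol also considers the risk minimal and reports no adverse effects in its healthy-volunteer trial, which limits the weight of the point.

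Third, a few days lies within a week, so the mismatch is small. That is fair, but the instruction bears on clinical evaluation and possible unblinding, and one wording costs nothing.

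Two stronger readings are tempting and are not supported:

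- A reader might infer that a planned active-versus-placebo safety comparison is biased. No post-treatment comparison is planned, only tabulation and review. On-treatment events are captured at the end of each block in both sequences, and the post-washout capture sets patients just off active against patients just off placebo.
- A reader might set the stated reassurance that "the dose of clonidine used is much lower than oral or transdermal preparations" against the composition in Interventions, where 0.1% W/V is 1 mg/ml and 1 ml three times daily is 3 mg applied per day. The documents give no oral or transdermal dose, so no contradiction can be shown. The same section already cites very low plasma levels after topical use.

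**Conclusion.** The point holds as a modest gap in safety collection plus a separate inconsistency of wording. On the visible text, solicited capture after stopping active drug covers an expected 16 of 32 patients (10 to 22 under the coin flip). With no events seen, solicited data would exclude withdrawal rates above about 17% rather than about 9%. That difference assumes a 16/16 split, no dropout, complete detection by the scheduled question and none by self-report, so the real loss at that split is smaller. The figures assume no true withdrawal rate, for which the documents give no basis. It is not shown that events will in fact be under-counted in the second sequence, only that they are sought less thoroughly there. The differing post-completion windows are plain on the page and do not depend on any of these assumptions. No view is taken here on which window is clinically right.

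**What to change.** 1. Reconcile Safety and adverse event outcomes with Endpoints and post-trial care so that both state one post-completion reporting window, of a defined length chosen by the sponsor.
2. Check Table 1 and the full protocol. If a contact after block 2 is already there, add it to the sentence in Study process. If not, add one scheduled adverse-event telephone contact for both sequences at the end of the chosen window, using the same questions as after washout.
3. Tabulate post-treatment events by the treatment just stopped, and mark each as solicited or self-reported. The marker also separates patients who finished before the change.

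The cost is one call per patient (at most 32) by the existing blinded coordinators, a short amendment through the ethics-board route described under Trial status, and slightly longer participation. That section describes the trial as still recruiting, so the change can help only patients not yet past the window.
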